# Cognitive training plus a comprehensive psychosocial programme (OPUS) versus the comprehensive psychosocial programme alone for patients with first-episode schizophrenia (the NEUROCOM trial): A study protocol for a centrally randomised, observer-blinded multi-centre clinical trial

**DOI:** 10.1186/1745-6215-12-35

**Published:** 2011-02-09

## Abstract

**Background:**

Up to 85% of patients with schizophrenia demonstrate cognitive dysfunction in at least one domain. Cognitive dysfunction plays a major role in functional outcome. It is hypothesized that addition of cognitive training to a comprehensive psychosocial programme (OPUS) enhances both cognitive and everyday functional capacity of patients more than the comprehensive psychosocial programme alone.

**Methods:**

The NEUROCOM trial examines the effect on cognitive functioning and everyday functional capacity of patients with schizophrenia of a 16-week manualised programme of individual cognitive training integrated in a comprehensive psychosocial programme versus the comprehensive psychosocial programme alone. The cognitive training consists of four modules focusing on attention, executive functioning, learning, and memory. Cognitive training involves computer-assisted training tasks as well as practical everyday tasks and calendar training. It takes place twice a week, and every other week the patient and trainer engage in a dialogue on the patient's cognitive difficulties, motivational goals, and progress in competence level. Cognitive training relies on errorless learning principles, scaffolding, and verbalisation in its effort to improve cognitive abilities and teach patients how to apply compensation strategies as well as structured problem solving techniques. At 16-week post-training and at ten-months follow-up, assessments are conducted to investigate immediate outcome and possible long-term effects of cognitive training. We conduct blinded assessments of cognition, everyday functional capacity and associations with the labour market, symptom severity, and self-esteem.

**Discussion:**

Results from four-month and ten-month follow-ups have the potential of reliably providing documentation of the long-term effect of CT for patients with schizophrenia.

**Trial Registration:**

Clinicaltrials.gov NCT00472862.

## Background

### Cognitive dysfunction in schizophrenia

Cognitive dysfunction plays a major role in functional outcome in schizophrenia [1-3]. Up to 85% of patients demonstrate cognitive dysfunction in at least one domain, and patients' performances on neuropsychological tests are typically in the range of 1 ½ to 2 standard deviations (SD) below norm [4-7]. Cognitive dysfunction associated with schizophrenia encompasses attention deficits, poor information processing, memory difficulties, and executive dysfunction leading to difficulties in learning and poor problem-solving abilities.

The cognitive impairments associated with schizophrenia are present prior to the onset of the psychotic symptoms of the illness, and seem to be relatively stable over time and independent of clinical state [8]. While antipsychotic medication may effectively reduce the clinical symptoms, cognitive dysfunction remains largely unaffected [9]. The cognitive impairments constitute a significant challenge for the treatment of schizophrenia, and are considered to be the greatest hindrance to psychosocial and vocational rehabilitation [10-12].

### Studies examining the effects of cognitive rehabilitation

Recognition of the impact of cognition on functioning in schizophrenia has given rise to the demand for intervention that directly targets cognitive dysfunction. A Cochrane systematic review from 2000 by Hayes and McGrath [13] included three small randomised clinical trials, which provided no conclusive evidence for or against cognitive training as a treatment for schizophrenia. In 2007, a meta-analysis of 26 randomised clinical trials by McGurk and coworkers [14] found a moderate effect of cognitive remediation on cognition, and a small to moderate effect on real-world functioning and symptoms.

The 2009 PORT working group review of psychosocial treatments for schizophrenia [15] concludes, however, that more research in the field of cognitive remediation is needed before a recommendation can be offered. Some of the shortcomings in earlier trials are short-term programmes and a lack of long-term follow-up examinations. The sustainability of improvements therefore remains an unanswered question. The variability of outcome measures used also complicates interpretation of findings. Thus, a consensus battery of outcome measures has been suggested by MATRICS [16] for future trials. Many studies of cognitive training (CT) were trials with small sample sizes, which limits the conclusions that can be drawn from the results [17]. Likewise, the question of generalisation is a central challenge in CT-studies: Although Dickinson et al. [18] find improvements on training tasks used in CT sessions, the effect does not generalise to other neuropsychological tests or functional outcomes.

There is a need for well-organised and sufficiently large randomised clinical trials of the effect of computer-assisted CT integrated in psychosocial rehabilitation. In order to examine to what extent CT improves the psychosocial rehabilitation and facilitates new learning, improvements in the level of neuropsychological performance as well as the level of everyday functional capacity must be identified and compared [16,19,20]. As recommended by Buchanan et al. [16], the NEUROCOM trial employs a prospective design and includes real-life outcome measures at both baseline, immediately after 16 weeks of training and at 10 months follow-up. By employing CT, we seek to secure individual adaptation and motivation through continuous evaluations and level adjustments between patient and trainer.

### Objectives

The overall objective of the NEUROCOM trial is to accept or reject the following hypotheses:

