#### Primary hypothesis

The effect on patients' functional capacity in daily life of a 16-week programme of computer-assisted CT integrated in OPUS is not different from OPUS alone [for a detailed description of the OPUS intervention see [21]], with regard to the primary response variable of everyday functional capacity as measured by a Danish adaptation of the brief version of the University of California San Diego Performance Skills Assessment (UPSA-B)[22,23].

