### Assessments

The first assessment occurs before randomisation, since information from the baseline assessment is used as stratification variables and to validate inclusion and exclusion criteria. At baseline, participants are administered the clinical version of WHO Present State Examination [54] and the Danish version of National Adult Reading Test [55,55], a widely used measure of pre-psychotic IQ. All other assessments are conducted in a fixed order at baseline, post-training, and at follow-up 10 months after inclusion, regardless of whether participants have followed the full training programme according to the intent-to-treat principle [i.e. [56]]:

• Functional capacity in two domains of daily life (finance and communication) assessed using the Danish version of UPSA-B [22,23].

• Neuropsychological tests of seven cognitive domains (see Table 1 Neuropsychological assessment tools used in the NEUROCOM trial.).

**Table 1 T1:** Neuropsychological assessment tools used in the NEUROCOM trial.

Domain of cognition	Tests
Speed of information processing	BACS Symbol Coding Category Fluency Trail Making A

Attention	Continuous Performance Test - Identical Pairs

Working memory	Wechsler Memory Scale-III Spatial Span Letter-Number Sequencing Trail Making B

Verbal learning and memory	Hopkin's Verbal Learning Test-Revised

Visual learning and memory	Brief Visuospatial Memory Test-Revised

Problem-solving	NAB Mazes Wisconsin Card Sorting Test, 64-card computerised version

Social cognition	Mayer-Salovey-Caruso Emotional Intelligence Test: Managing Emotions (MSCEIT)

Pre-psychotic IQ *	Danish National Adult Reading Test (DART) *

* Only assessed at baseline.

• Positive and negative symptoms evaluated with Positive and Negative Symptom Scale (PANSS, [57].

• Danish version of Rosenberg's Self-Esteem Scale [28,28].

• Assessment of occupational status and/or educational activities.

• Type and dose of antipsychotic medication (chlorpromazine equivalents).

• Participation in CBT or SST group treatment.

• Number of psychiatric hospitalisations.

• Sociodemographic variables: education, living status, economic conditions, relationships (partner, number of close friends) and number of children.

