### Sample size estimation

The power of the study is set at 90%, i.e., beta = 0.1. Alfa is set at 0.05. The primary outcome UPSA-B consists of 1-point-items, and every item has a face validity of real-world significance, i.e. correctly performing an emergency call or correctly remembering a scheduled appointment. On that premise the minimal relevant difference (MIREDIF) is set at one point on UPSA-B total score (Mean = 17.63 points, SD = 1.66) [23,59]. We assumed the SD to be 1.66. To be able to detect a difference of one point on UPSA-B mean total score between the two groups, the required number of participants in each group is 31 or 62 in total. Estimated dropout of 45% necessitates recruitment of about 120 participants, 60 in each intervention group.

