### Statistical analysis

Continuous outcome measures will be analysed with repeated measurements in a mixed-effects model and performed using SPSS 17.0. Logistic regression analyses will be applied with binary outcome measures. Dosage of antipsychotic medication (in chlorpromazine equivalents) will be included as a covariate variable in the analyses. Dropout analysis will be carried out, comparing baseline values for participants who drop out of intervention with those who follow the entire intervention. Baseline values of measures will be included in the analyses whenever possible.

Data sets on non-completing participants will be included in the data analyses on an intention-to-treat basis. In case of non-existent outcome measures (withdrawal, dropout, lost to follow-up), the pattern of missing data and the assumption of missing data at random (MAR) will be explored. If data distribution is skewed, repeated-measurements analyses will be performed.

The primary outcome measure, performance on UPSA-B, will be analysed, like other continuous outcome measures, in a repeated-measurements model with unstructured variance matrix. This approach assumes that the distribution of missing data can be estimated from the information from previous interviews and from information about other patients in the database. The condition for using this method is the assumption that data are missing at random when taking into consideration the information extracted from baseline interviews and information about the other patients in the database. In this model, baseline values of the scales are included [60,61]. Variables included as covariates will be site (Aarhus/Copenhagen), level of education, pre-psychotic IQ (DART), baseline values of secondary verbal memory, and the baseline values of variables that differ significantly in dropout analyses.

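### The objective allows null hypotheses to be accepted although the trial is a superiority design with no equivalence margin, and no deciding visit or overall contrast is named for UPSA-B

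*Protocol article*

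**What the plan says.** The Objectives section opens with: "The overall objective of the NEUROCOM trial is to accept or reject the following hypotheses". The primary hypothesis is then worded as a null: "The effect on patients' functional capacity in daily life of a 16-week programme of computer-assisted CT integrated in OPUS is not different from OPUS alone". The secondary and tertiary hypotheses take the same form. The only threshold is in Sample size estimation, where "the minimal relevant difference (MIREDIF) is set at one point on UPSA-B total score"; it serves there as a difference to detect. No margin for concluding no difference is given, and no rule for reading a confidence interval.

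On timing, Assessments says: "All other assessments are conducted in a fixed order at baseline, post-training, and at follow-up 10 months after inclusion". UPSA-B is among these assessments. The Abstract gives the two later visits different purposes without ranking them: "At 16-week post-training and at ten-months follow-up, assessments are conducted to investigate immediate outcome and possible long-term effects of cognitive training". The primary hypothesis names no assessment time; the 16 weeks it mentions is the length of the programme. Statistical analysis puts UPSA-B "in a repeated-measurements model with unstructured variance matrix" but states no visit, contrast or overall test for the primary hypothesis. Alpha appears once: "Alfa is set at 0.05".

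**The concern.** Two things are left unsettled in how the primary hypothesis will be decided.

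First, accepting a null of no difference means concluding that cognitive training adds nothing to OPUS. A superiority test can reject that null or fail to reject it; failing to reject does not establish it. If the objective is followed literally, a trial whose interval still contains one UPSA-B point could be reported as showing no effect. The Discussion says the results should inform whether training is extended to clinical practice, so this would matter.

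Second, with two post-baseline visits, one alpha and no named primary test, a significant result at either visit could be presented as confirming the primary effect.

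**Working it through.** **Inputs.** From Sample size estimation: SD 1.66, minimal relevant difference 1 point, alpha 0.05 (two-sided assumed from the form of the hypothesis), power 90%, 31 per group required, 45% dropout, about 120 recruited. Evaluable number: 120 × 0.55 = 66, or 33 per group. The article gives neither a baseline-outcome correlation nor a between-visit correlation; those below are assumptions.

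**The plan's own figure.** n per group = 2 × 1.66² × (1.960 + 1.282)² / 1² = 57.9, so 58. The stated 31 is not reproduced as a two-group comparison. This is a separate matter, but it affects the results below.

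**Precision, unadjusted, 33 per group.**
- Standard error = 1.66 × √(2/33) = 0.409.
- Half-width = t(0.975; 64 df) × 0.409 = 1.998 × 0.409 = 0.816.
- A difference is non-significant below 0.816. Its upper limit stays below 1 only if the difference is below 1 − 0.816 = 0.184.
- Non-significant differences between about 0.18 and 0.82 therefore leave one point inside the interval.

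**Precision with baseline adjustment.** The standard error is multiplied by √(1 − r²), where r is the baseline-outcome correlation. At r = 0.7 the factor is 0.714, the half-width is 0.58, and the range is 0.42 to 0.58.

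**Chance of accepting the null when the true difference is one point, 33 per group.**

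| Assumed r | Half-width | Non-significant differences that include 1 point | Null accepted |
|---|---|---|---|
| 0 | 0.82 | 0.18 to 0.82 | 33% |
| 0.5 | 0.71 | 0.29 to 0.71 | 21% |
| 0.6 | 0.65 | 0.35 to 0.65 | 15% |
| 0.7 | 0.58 | 0.42 to 0.58 | 8% |
| 0.8 | 0.49 | none | 2% |

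The range disappears once the half-width is below 0.5, because every non-significant result then has an upper limit below 1. At 33 per group that needs r of about 0.79 or more. With no dropout (60 per group), the unadjusted half-width is 1.980 × 1.66 × √(2/60) = 0.60, the range is 0.40 to 0.60, and the null is accepted in about 9% of trials.

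**Two visits.** Under the null, take two standard normal test statistics with correlation ρ and claim success if either exceeds 1.96 in absolute value:
- ρ = 0.5: 9.1%
- ρ = 0.7: 8.3%
- ρ = 0.8: 7.8%

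A single overall treatment test from the mixed model, or one named visit, gives 5%.

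**The case against.** Accepting or rejecting is conventional language for a null hypothesis. Nothing in the article says that a non-significant result will be reported as proof of no effect. The Abstract states a superiority hypothesis, and the Discussion is cautious about a null result: it warns that training effects may be hard to discern against OPUS and that OPUS may create a ceiling. This stands against the stronger reading. A reader might infer that the investigators plan to treat non-significance as proof, but the document does not say so. What remains is that accepting the null is part of the stated objective and no other text says how a non-significant result will be read.

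The 33% is unadjusted, assumes the full 45% dropout, and mainly reflects the sample-size shortfall: at the stated 90% power the figure would be 10%. The plan includes baseline values in the model, and patients with only one follow-up visit also contribute. This stands too, and 33% should not be quoted alone.

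On the visits, a reader might infer that the plan tests each at 5% and claims success on either. It does not say that. One mixed model is planned, and an overall test from it would hold 5%. The detail of a contrast is often left to an analysis plan. But which visit or overall effect decides the primary hypothesis is part of that hypothesis, and the article fixes the hypothesis, alpha, model and sample size while leaving this open in all of them.

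**Conclusion.** The concern holds in a limited form. As worded, the objective permits a conclusion that the design cannot support. Unless the baseline correlation is high (about 0.79 or more at 33 per group), some non-significant results would leave the protocol's own one-point difference inside the interval. If the true difference is one point, the null would be accepted in about 33% of trials unadjusted and about 8% at an assumed correlation of 0.7.

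The missing primary test opens the way to a type I error of about 8-9%, but only under an either-visit rule that the plan does not state. It is a possibility to be closed, not a demonstrated inflation. All figures rest on SD 1.66 and on the assumed correlations shown.

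**What to change.** - In Objectives, replace the accept-or-reject wording by reject or not reject.
- Tie the conclusion to the 95% confidence interval: state no relevant difference only if the interval excludes one UPSA-B point. Call any other non-significant result inconclusive.
- Before unblinding, name one primary test for UPSA-B: either one visit or one overall treatment contrast from the mixed model. The choice is the sponsor's. There is a trade-off, because the Background and Discussion present long-term effect as the trial's contribution, so the documents do not settle the matter in favour of 16 weeks.
- If one visit is named, test the other only if the first is significant.

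The cost is wording in the objectives and the analysis section, with no new data or patients. The downside is that an effect seen only at the non-primary visit would count as secondary.

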#### Primary hypothesis

The effect on patients' functional capacity in daily life of a 16-week programme of computer-assisted CT integrated in OPUS is not different from OPUS alone [for a detailed description of the OPUS intervention see [21]], with regard to the primary response variable of everyday functional capacity as measured by a Danish adaptation of the brief version of the University of California San Diego Performance Skills Assessment (UPSA-B)[22,23].

#### Secondary hypotheses

The effect on patients' cognitive functioning of a 16-week programme of computer-assisted CT integrated in OPUS is not different from OPUS alone, with regard to the secondary response variable of seven domains on neuropsychological tests as recommended by MATRICS [24,25], Trail Making B [26], and a computerised 64-card version of Wisconsin Card Sorting Test [27].

#### Tertiary hypothesis

The effect of a 16-week programme of computer-assisted CT integrated in OPUS is not different from the OPUS intervention alone in terms of patients' association with the labor market and self-esteem, measured by occupational status and Rosenberg's Self-Esteem Scale [28].

## Methods

### Randomisation

The NEUROCOM study is a randomised parallel-group clinical trial in which participants are randomly allocated to experimental intervention versus standard intervention (Figure 1**Flowchart of the NEUROCOM trial**. See text for further information.). The centralised, stratified block-randomisation 1:1 is carried out by Copenhagen Trial Unit (CTU) following two stratification criteria: Performance level on UPSA-B (good: total raw score ≥ 16 or poor: total raw score < 16), and participation in OPUS cognitive-behavioral therapy (CBT) group or social skills training (SST) group (yes or no). The generation of allocation sequence is computerised. Allocation concealment is achieved through centralised randomisation with a block-size unknown to investigators.

**Figure 1 F1:**
[figure not shown]
**Flowchart of the NEUROCOM trial**.

Patients being considered for inclusion in NEUROCOM will obtain a consecutive participant number. Each investigator will obtain a four-digit pin code by calling the CTU. By use of this pin code, the investigator can call CTU and request a randomisation in NEUROCOM. The investigator then informs about NEUROCOM, CPR-number [for explanation see [29]], UPSA-B ≥ or < 16, and SST/CBT group yes/no. The CTU provides a three-digit randomisation number.

### Blinding

The CTU then informs the cognitive trainers of the participant's name, CPR-number, randomisation number, plus the intervention arm via fax. The cognitive trainers inform the individual participant which intervention programme he or she has been allocated to. The trial is not blinded with regard to participants, cognitive trainers, and OPUS teams. Blinding applies to the raters engaged in the outcome assessment. In the follow-up assessments, the participants are instructed in advance not to reveal what type of intervention they have received. Blinding also applies during data analysis, i.e., the randomised intervention allocation is concealed until the statistical analyses of the data have been completed.

### Participants

Patients are recruited from OPUS, which is implemented as a standard programme for young adults with first-episode psychosis in Copenhagen and Aarhus. The OPUS staff recruits patients to the NEUROCOM trial. Independent assessors interview the referred patients and evaluate the following inclusion and exclusion criteria.

#### Inclusion criteria

Participants are outpatients, aged 18-35 years, diagnosed with first-episode psychosis or schizotypal disorder within F2 spectrum in ICD 10 http://www.who.int/classifications/icd/en/. Participants are in a post-acute phase of illness, have sufficient comprehension of Danish (i.e., do not need an interpreter), and provide written informed consent.

#### Exclusion criteria

Exclusion criteria are rejection of participation, organic disorder, or abuse of psychoactive drugs.

### Interventions

#### Experimental intervention

Under a pilot study, a first version of a manual was developed for a 16-week CT programme for patients with schizophrenia [30,30].

For one hour twice a week for 16 weeks, participants engage in computer-assisted CT plus one competence dialogue every other week. The competence dialogues function as bridging between CT sessions and the participant's development of everyday life competencies. Training consists of four modules: the first three modules cover the areas of attention, memory, and executive functions, and the last module focuses on the cognitive area and related tasks, which the individual participant prefers or needs to improve: Thus, the content of module 4 is based on both the participant's and the trainer's judgment.

Training contains exercises of simple attention, attention span and vigilance, planning, problem solving, interaction-based training of working memory, and verbal and visual long-term memory.

Module 1 and 2 are based on non-social cognitive tasks on a gradually increasing level of difficulty, using COGNIsoft computer tasks [31], whereas module 3 and 4 include practical everyday tasks. This order of modules is in keeping with the notion of a hierarchy of cognitive functions [12], calling for training of elementary attention and working memory functions before addressing more complex problem-solving skills. In their review, Twamley et al. [32] stress the importance of directly targeting the participant's everyday functioning. Thus, calendar training is a vital part of this intervention: a way of addressing common difficulties of memory and planning ability by explicitly teaching compensatory strategies. A recent report from a working group of cognitive remediation trials underscores the importance of considering individual abilities, addressing motivation, and providing bridging facilities that allow participants to apply newly acquired skills [33,34]. Calendar training and competence dialogues are intended to support environmental adaptation and transference of learning.

Training relies on errorless learning principles, scaffolding, and strategy-learning as recommended by Wykes and van der Gaag [35] and van der Gaag et al. [36]. Positive reinforcement, modeling, and verbal instructions are widely used. Trainers describe the structure and explain the purpose of training exercises at the beginning of every session, in order to provide a consistent learning environment.

A review of cognitive rehabilitation trials underscores the importance of possibilities for individual adjustments [37]. CT is therefore carried out individually with continuous progress evaluation between participant and trainer.

Trainers are occupational therapists and psychologists at bachelor or master level with psychiatric experience. Knowledge has been exchanged throughout the process of the pilot study about cognitive dysfunction in schizophrenia. Trainers were introduced to errorless learning principles, and didactic instruction in the manualised CT has been carried out at meetings during preparation of the NEUROCOM study.

Much empirical research in psychosocial interventions for schizophrenia has shown that training in symptom handling, social proficiency training, and supportive provisions in occupational relations can help patients to function in their daily lives [38-47]. According to Bell et al. [48], there is sufficient evidence that the *combination *of CT and psychosocial treatment, rather than individually occurring initiatives, has the greatest potential for promoting outcome [see also [49,50]]. CT is therefore added to the comprehensive psychosocial programme OPUS.

The OPUS programme consists of affiliation with a primary patient manager, who provides contact on a weekly basis, involves the family, and provides the opportunity for psychoeducation and social skills training [for further details see [51-53]]. Depending on individual needs, patients are offered to take part in group therapy and either social skills training (SST) or cognitive-behavioral therapy (CBT). Participation in SST or CBT can be beneficial for both cognition and everyday functioning. To ensure comparability between the participants in the NEUROCOM trial, we stratify participants according to group therapy (SST/CBT) yes/no before allocation to experimental intervention (CT) versus standard OPUS.

